#### 95 *Sample Size*

96 We estimate a moderate effect size of 0.60 will be reported at week 12. Assuming a type-1  
97 error of 5%, we will need to follow up 120 patients across the two groups to achieve 90%  
98 power at Week 12. With an anticipated dropout rate of 20% by Week 12, we will randomise  
99 150 participants. An effect size of 0.4 or greater for difference in MADRS scores in  
100 randomised controlled trials of antidepressants versus placebo has been suggested as  
101 necessary to suggest clinical utility for an antidepressant used as monotherapy. A sample of  
102 120 participants is therefore powered to detect moderate to large effect sizes and trends  
103 towards significance in areas of smaller effect.

104

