#### *Statistical Analysis*

Initial descriptive analysis will be conducted to study the profile of the subjects and investigate group differences at baseline on main demographics and clinical measures. Frequencies and proportions will be used for categorical variables and mean and standard deviations, median and inter-quartile range, minimum and maximum for continuous variables. No statistical significance tests will be used to compare groups. Drop out, visit frequency and adherence to treatment will be summarized by group with the appropriate descriptive statistics.

The main analysis will follow the Intention-to-treat (ITT) principle in which subjects are assigned to treatment groups as randomized. Subjects that drop out of the study will be included in the analysis provided that they have a baseline score for the outcome. For the primary hypothesis, the MADRS scores at week 12 will be compared between groups using a mixed effect model. The outcome for the model will be all post-baseline MADRS scores and the fixed effects will include baseline MADRS scores, treatment group, time (post-baseline timepoints) and a treatment group by timepoint interaction. To account for the dependencies between repeated measures on the same patients, an intercept for each individual will be included as a random effect. A linear contrast will be used to test the primary hypothesis, the difference between groups in at week 12 in MADRS scores. Given the modest sample size it will likely not be possible to use as random slope for each subject, however the covariance matrix of the residuals of the model can be allowed to correlate to account for dependencies across time. Two tailed tests and an alpha level of 0.05 will be used for significance. All estimates will be presented with the 95% confidence interval. To give an estimate of effect size, standardized regression coefficients will be calculated using the overall SD of the baseline outcome scores as the metric. One advantage of this approach is it gives the magnitude and direction of effect in units of patient population of interest.

275

276 Secondary analyses will use similar mixed models to that of the primary outcome, baseline  
277 adjusted with time, treatment group and the interaction between treatment group and time as  
278 independent variables. As for the primary outcome, the main timepoint of interest is 12 week  
279 follow up and treatment effects will be determined by contrasts at the measured timepoint.  

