280 To compare response and remission rates between groups logistic regression will be used in  
281 which patients will be classified as in remission or not according to standard criteria on the  
282 MADRS scale. As there are multiple measures, p values will be adjusted for multiple  
283 comparisons using a correction based on controlling the family-wise error. Outcomes at  
284 timepoints other than 12 week follow-up will be considered exploratory and the main focus  
285 will be effect sizes (standardized regression coefficients).

286

287 To compare frequency of adverse events descriptive summaries will be presented by  
288 treatment group. Differences in the rates of AEs will be assessed by generalized linear mixed  
289 model with Poission or negative binomial distribution will be used given sufficient numbers  
290 of events, where time, treatment group and their interaction are fixed effects with subjects as  
291 random effects. Alternatively, simple count models will be used at each timepoint given the  
292 limited sample size and complexity of GLMM models.

293

294 It is likely there will be some drop-out of participants from the trial. Baseline predictors of  
295 missingness can be identified using logistic regression with the outcome (missing or not).  
296 Mixed effect models fitted through maximum likelihood can use all available information in  
297 the data potentially avoiding removal of dropout subjects from the analysis. Moreover, by  
298 including baseline predictors of missingness in the statistical models, the analysis may

assume the data to be missing at random (MAR). Diagnostic analysis will be conducted through checking residuals for outliers, influential data points and normality. If outliers or influential points are found a sensitivity analysis will be conducted after removing such points to see if the main findings change.

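### The protocol leaves open whether covariates found by screening observed dropout enter the primary model, and it rests MAR on baseline predictors, which can support that assumption but cannot establish it.

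*Protocol*

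**What the plan says.** The Statistical Analysis section of the protocol defines the primary analysis as a mixed model for all MADRS scores after baseline. It has four fixed-effect terms (baseline MADRS, arm, visit, and arm by visit) and a random intercept per patient, and the test is the week-12 contrast.

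The paragraph on dropout in the same section says of baseline predictors that "missingness can be identified using logistic regression with the outcome (missing or not"). It appeals first to maximum likelihood, which uses every recorded score. It then adds that by "including baseline predictors of missingness in the statistical models, the analysis may" "assume the data to be missing at random (MAR"). It gives no list of candidates and no selection threshold, and it does not say which models are meant. The one sensitivity analysis named is refitting without outliers or influential points.

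Three other places bear on this:
- The criteria for leaving the study, under Exclusion Criteria, include adverse events and poor compliance. Compliance is judged on study medication taken between visits.
- Randomisation and Allocation Concealment stratifies by centre and by baseline severity. Centre is not among the listed fixed effects.
- Sample Size says "We estimate a moderate effect size of 0.60 will be reported at week 12" and "With an anticipated dropout rate of 20% by Week 12, we will randomise" 150.

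**The concern.** There are two separate problems.

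**The model.** One paragraph gives a list of fixed effects. A later one lets further covariates, chosen by looking at who dropped out, into models it does not name. Two competent analysts could fit different primary models and both claim to follow the protocol.

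**The ground for MAR.** MAR is a condition on everything observed, including post-baseline data. A baseline covariate can account for dropout that is predictable at baseline. It cannot account for a patient who leaves at week 6 because of tolerability, or because mood worsened after the last rating. The withdrawal criteria create exits of this post-baseline kind, so the supplement that the protocol offers does not reach them.

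At stake is how far the week-12 contrast can be trusted when about one patient in five has no week-12 score, particularly if leavers differ between the arms.

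**Working it through.** **1. The plan's own figure.** Inputs from the protocol: effect 0.60 SD; "Two tailed tests and an alpha level of 0.05 will be used for significance"; 90% power; 20% dropout.
- n per arm = 2(1.960 + 1.282)² / 0.60² = 58.4, so 59 per arm (118 in all). The protocol's 120 gives 90.8% power by the normal formula and 90.3% by the noncentral t.
- 120 / (1 − 0.20) = 150.

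The stated sample size reproduces.

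**2. What baseline adjustment does and does not cover.** A large simulation (200,000 patients, baseline and four visits, about 20% overall dropout) used a likelihood analysis with unstructured covariance by arm. The baseline score was in every model. The strength of dropout, a log-odds of 1 or 2 per SD, and the visit correlations are assumptions. Negative values favour simvastatin.

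| Dropout depends on | True 0 estimated as | True −0.60 estimated as |
|---|---|---|
| baseline score | −0.01 to 0.00 | −0.60 |
| last recorded score | 0.00 | −0.61 to −0.60 |
| current unrecorded score, same direction in both arms | 0.00 to 0.01 | −0.58 to −0.54 |
| current unrecorded score, opposite directions by arm | −0.12 to −0.21 | −0.72 to −0.82 |

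The likelihood analysis is sound in the first two rows. In the third the bias is small and towards zero. Only the fourth produces an apparent benefit, and having the baseline score in the model did not remove it.

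**3. What covariate selection does.** In 4,000 simulated null trials (150 patients, 10 candidate covariates, selection at p < 0.05 against missingness; both settings are assumptions), a week-12 ANCOVA gave these type I error rates:
- fixed covariates: 4.4%
- missingness-selected covariates: 4.6%
- the more favourable of the two models reported: 5.8%

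The Monte Carlo standard error is 0.34 percentage points.

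**4. How much departure from MAR would matter.** Let active-arm leavers be δ SD worse than MAR predicts, with a proportion p = 0.20 leaving. The effect becomes d − pδ. The critical difference at 60 per arm, unadjusted, is c = 1.96 × √(2/60) = 0.358 SD. Significance is lost at δ = (d − c)/p:
- d = 0.40: (0.40 − 0.358)/0.20 = 0.21 SD
- d = 0.50: (0.50 − 0.358)/0.20 = 0.71 SD
- d = 0.60: (0.60 − 0.358)/0.20 = 1.21 SD

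With the t critical value (c = 0.3615) these are 0.19, 0.69 and 1.19.

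Baseline adjustment shrinks c by √(1 − r²), where r is the correlation of baseline with week-12 MADRS. The protocol gives no r. For r = 0.3, 0.5 and 0.6, c is 0.341, 0.310 and 0.286. The tipping point at d = 0.40 then rises to 0.29, 0.45 and 0.57 SD.

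**The case against.** The best defence is that the passage is permissive and modest. It says predictors can be identified and that MAR may be assumed, and it nowhere says that MAR has been secured. It leads with maximum likelihood on all post-baseline scores, with MADRS scheduled at weeks 2, 4, 8 and 12, so dropout that follows recorded mood is already handled. Baseline predictors are offered as a supplement, which is reasonable practice. The screen needs only baseline data and missingness status, and investigators stay masked until database lock, so it need not involve allocation. Selection rules are often left to the SAP.

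Most of this stands, and it rules out several stronger readings that a reader might infer:
- *That the primary covariates will be chosen from the data.* The text allows this but does not require it.
- *That such selection distorts the test.* It did not in simulation (4.6% against 4.4%). The 5.8% needs someone to report the better of two models, which the protocol does not propose.
- *That the lack of an analysis under informative dropout is itself a defect.* Such analyses commonly sit in the SAP, which is not at hand.

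What the defence does not answer is that the protocol names one set of fixed effects and then allows others without saying where they apply. Nor does it show how baseline variables could cover the post-baseline exits that the protocol describes.

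**Conclusion.** The point holds in a limited form. The primary model is not uniquely fixed by the protocol text, and the reason given for assuming MAR is insufficient.

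The harm from the open model is a matter of discretion and is small in size. The harm from unrecorded-score dropout is mainly a concern when it differs by arm: 0.12 to 0.21 SD of spurious benefit under a true null when the arms run in opposite directions, and none to speak of when they run alike.

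It would be wrong to conclude that the trial is fragile at its design effect. At an observed 0.60 SD, active-arm leavers would have to be about 1.2 SD worse than MAR predicts before significance is lost. An observed effect near 0.40, the value that Sample Size links to clinical utility, is more exposed, at about 0.2 SD or somewhat more after baseline adjustment.

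These figures assume 20% dropout in the active arm, placebo-arm leavers as MAR predicts, and a standard error held at 60 per arm. The simulated bias also rests on the assumed correlations and dropout strengths, and on an unstructured covariance rather than the protocol's random intercept.

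**What to change.** Make three wording changes in the Statistical Analysis section:

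1. State that the primary model's covariates are fixed before unblinding as baseline MADRS plus the randomisation stratification factors. That means centre, and baseline severity to the extent that baseline MADRS does not already carry it.
2. State that covariates selected because they predict missingness are used only in a sensitivity model.
3. Replace the sentence on MAR with a plain statement that the primary analysis assumes MAR, which the data cannot verify.

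Then confirm that the SAP contains a delta-adjusted analysis in which active-arm leavers are made progressively worse than MAR predicts. Add one if it does not.

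The cost is wording plus at most one extra analysis, with some programming. The downside is that the result may look less robust when reported.

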#### *Exclusion Criteria*

Primary psychotic disorder or bipolar disorder; history of intolerance to statins or presence of any contraindication to statins; presence of any serious medical condition or neurological problem; presence of autoimmune or inflammatory disorder (e.g. systemic lupus

erythematous, rheumatoid arthritis and inflammatory bowel disease); alcohol or drug dependence; active suicidal ideation; pregnant or breast-feeding. Patients with a serum low density lipoprotein (LDL) level of <80 mg/dL at baseline are also excluded from the study as are patients with abnormal hepatic enzymes (Aspartate transaminase (AST) and Alanine transaminase (ALT)) or abnormal Lactate Dehydrogenase (LDH) or Creatinine Phosphokinase (CPK) values at baseline. Patients already on statin treatment will also be excluded.

The criteria for leaving the study are: (1) at the participant's request; (2) at the discretion of the responsible physician or trial investigator (e.g. an adverse event, poor compliance). Poor compliance is defined as either taking <75% of study medication between assessments points at baseline, week 2, 4, 8 and 12 or missing trial medications all together for  $\geq 7$  days in period (3) pregnancy.

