The exploratory hypothesis that baseline lipid/CRP levels will affect response to simvastatin will be tested by adding the baseline lipid/CRP to a model for the primary outcome at 12 weeks, adjusted for baseline and including a treatment group by baseline lipid/CRP. The lipid/CRP level will be considered moderators if interaction with treatment group is significant (at significance level of 0.05, using bootstrapping for inference and construction of confidence intervals). If this is the case, exploratory plots that look at the group effect at different levels of the moderators will be used to study the nature of the moderation.

In order to test the hypothesis that changes in peripheral levels of lipids/CRP will be a mediator in the path between treatment and change in MADRS scores, an initial descriptive analysis will be conducted to look at the bivariate association between treatment group and change in lipid/CRP levels, and between change in lipid/CRP (at 4 and 12 weeks) and change in MADRS scores. A mediation model will then be fitted to the data that joint models the effects of treatment on the change in lipid/CRP at 4 weeks and MADRS at 12 weeks. The mediation effect is tested by the proportion of the total effect from treatment group to change in MADRS that goes through change in lipid/CRP. This model will be fitted in Lavaan in R or Mplus 7.11[35] and the indirect effect estimated through bootstrap resampling. Given the sample size, note the effect sizes for the indirect mediation pathway would need to be relatively large [36].

323

324 *Safety Monitoring*

325 Adverse events monitoring from the time informed consent is obtained until follow-up at 12  
326 weeks (using the side effect assessment scale). Laboratory parameters including total serum  
327 cholesterol, LDL, HDL, triglyceride, AST, ALT, LDH and CPK will be checked by the study  
328 physician before patient entry into the trial, and if there are any safety issues for which the  
329 patient should not be started on study medication, he/she will not be included to the study.

330

331 *Study coordination*

332 Local investigators will chair a weekly meeting with research assistants to help coordinate the  
333 study. The chief investigator will hold meetings with the research team every two weeks via  
334 Skype.

335

336 *Data protection and confidentiality*

337 For data security, consent forms and paper copies of assessment tools having any identifying  

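### The moderator label and the plots of effect by marker level depend on an interaction p<0.05 that a trial of this size reaches only for fairly large interactions; show every marker instead

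*Protocol*

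**What the plan says.** The Protocol's Statistical Analysis section introduces the moderation analysis as "The exploratory hypothesis that baseline lipid/CRP levels will affect response to simvastatin". The week-12 primary outcome is modelled with adjustment for baseline, the baseline marker and a treatment-by-marker interaction. The decision rule follows: "The lipid/CRP level will be considered moderators if interaction with treatment group is significant", judged "at significance level of 0.05, using bootstrapping for inference and construction of confidence intervals". The display depends on the same test: "If this is the case, exploratory plots that look at the group effect at different levels of the moderators will be used".

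Three other statements bear on this:

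- The same section makes a general promise: "All estimates will be presented with the 95% confidence interval".
- For outcomes at timepoints other than week 12, also exploratory, it puts the main focus on effect sizes.
- For mediation it adds a caution: "Given the sample size, note the effect sizes for the indirect mediation pathway would need to be relatively large". The moderation paragraph has no such caution.

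Measurement of biomarkers names the markers as HDL, LDL and CRP. Sample Size plans for a main effect of 0.60 with 120 patients followed up and gives no interaction size.

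**The concern.** A significance threshold is a poor filter for exploratory results when the test has limited power. It does two things here. A real interaction of modest size will often fail the threshold, and its marker will then be left unlabelled and unplotted. An interaction that passes will on average look larger than it is, because only large estimates can pass.

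Plots of the treatment effect against marker level are what most readers use to judge whether benefit varies between patients. If they appear only for markers that passed, the published picture is a selected one. A marker that did not pass is then easily read as shown not to matter.

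**Working it through.** **Inputs from the Protocol.** Sample Size: effect 0.60, type-1 error 5%, 90% power, 120 followed up, 20% dropout, 150 randomised. Methods: 75 per arm. Statistical Analysis: "Two tailed tests and an alpha level of 0.05 will be used for significance".

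**The plan's own figure.**
- Per arm, n = 2 × (1.960 + 1.282)² / 0.60² = 58.4, so 59, or 118 in total.
- With 60 per arm, power is 90.8% (normal) or 90.3% (noncentral t).
- 120 / 0.80 = 150.

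The stated numbers reproduce, but they concern the main effect only.

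**Assumptions, not in the Protocol.** The marker is continuous, expressed in SDs of the analysed sample, and acts linearly. The outcome is in week-12 MADRS SDs. The residual SD s is 1.0, or 0.866 if baseline MADRS correlates 0.5 with week 12 (√(1 − 0.5²) = 0.866). The true interaction δ is set to several values because the Protocol names none.

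**Standard error.** With equal arms, SE = 2s/√N. At N = 120:
- s = 1.0: SE = 2/10.954 = 0.183
- s = 0.866: SE = 1.732/10.954 = 0.158

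**Smallest estimate that can be significant.** 1.96 × SE = 0.36 (s = 1.0) or 0.31 (s = 0.866). These are normal-theory values; a bootstrap test will differ slightly. A true interaction of exactly this size has power of about 50%.

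**Detectable with 80% power.** 2.80 × SE = 0.51 or 0.44.

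**Power and overstatement.** Let λ = δ/SE and c = 1.96.
- Power = [1 − Φ(c − λ)] + Φ(−c − λ).
- Overstatement is the mean absolute estimate among significant results, divided by δ. It equals {λ[1 − Φ(c − λ)] + φ(c − λ) − λΦ(−c − λ) + φ(c + λ)} / (λ × power).

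Example with δ = 0.2 and s = 1.0: λ = 1.095, power = 0.195, overstatement = 2.29.

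| True interaction (SD per marker SD) | Power, s = 1.0 | Power, s = 0.866 | Overstatement, s = 1.0 | Overstatement, s = 0.866 |
|---|---|---|---|---|
| 0.2 | 20% | 24% | 2.3 | 2.0 |
| 0.3 | 38% | 48% | 1.6 | 1.4 |
| 0.4 | 59% | 72% | 1.3 | 1.2 |
| 0.5 | 78% | 88% | 1.14 | 1.07 |

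**Simulation check.** Least-squares fits with s = 1.0 and 6,000 runs per size gave power of 17.8%, 36% and 57% for 0.2, 0.3 and 0.4, with overstatement of 2.3, 1.6 and 1.3. This agrees with the formulas.

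**If all 150 patients contribute.** At s = 1.0, power is 23%, 45% and 69% for 0.2, 0.3 and 0.4, and overstatement is 2.1, 1.5 and 1.2. At s = 0.866, power is 29%, 56% and 81%, and overstatement is 1.8, 1.3 and 1.1. The pattern is milder but the same.

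**The case against.** The best defence is that much of the remedy is already planned. Estimates are promised with 95% intervals, and bootstrap intervals are specified for this very analysis. In a linear interaction model the coefficients give the estimated treatment effect at any marker level. The analysis is openly exploratory, and Sample Size already says that the trial is powered for moderate to large effects. All of this stands. It confines the point to the label and the plots, and it rules out the inference that non-significant interactions would go unreported. It does not justify making those two items depend on p<0.05, and exploratory status is a reason to show all the estimates.

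A reader might infer three stronger things that the Protocol does not support.

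- *That the rule misses most useful interactions and doubles those it keeps.* The Protocol names no useful interaction size. Power is below one half only for true interactions under about 0.31 to 0.36, and a doubling arises only near 0.2. Around the planned 0.60, an interaction of 0.2 gives effects of 0.4 at −1 SD and 0.8 at +1 SD (0.60 ± 0.2). Both meet the 0.4 benchmark that Sample Size cites for monotherapy. An interaction of 0.4 gives 0.2 and 1.0, and its power is 59-72%.
- *That the LDL entry criterion weakens the LDL test further.* Exclusion Criteria states: "Patients with a serum low density lipoprotein (LDL) level of <80 mg/dL at baseline are also excluded from the study". The loss depends on an LDL distribution that the Protocol does not give. With the marker in SDs of the enrolled sample, the restriction is already absorbed in the figures above.
- *That the rule undermines the precision-medicine aim in the Discussion.* That sentence concerns reductions in the markers being associated with response, not baseline levels as moderators.

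**Conclusion.** The point holds in a limited form. The Protocol lets a single significance test decide which markers are called moderators and which are plotted, and for interactions of 0.2 to 0.3 SD per marker SD that test fails more often than it succeeds. Markers that pass at those sizes carry estimates about 1.4 to 2.3 times too large. At 0.4 and above the test succeeds more often than not and the overstatement is 1.3 times or less.

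These figures rest on 120 evaluable patients, equal arms, a linear effect of a continuous marker and a residual SD of 0.87 to 1.0. The interaction sizes are illustrations. The primary analysis and the sample size are unaffected. This is a small, cheap improvement to an exploratory analysis.

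**What to change.** In the moderation paragraph of Statistical Analysis, replace the significance rule with estimation:

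- For each pre-specified baseline marker (HDL, LDL, CRP), report the treatment-by-marker interaction with its planned 95% bootstrap interval.
- For each marker, plot the treatment effect with its interval across the observed range, whatever the p-value.
- State that a non-significant interaction is not evidence that moderation is absent.

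This carries the Protocol's emphasis on effect sizes for its other exploratory results over to moderation. It needs no extra patients or data. The cost is revised wording, a few more plots and the loss of a simple yes/no label for each marker.

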45 paralysis, fatigue and interpersonal sensitivity [15, 16]. Hence lipid-lowering effects of statins  
46 may also play a role in putative antidepressant effects of this class of drugs. Data from the  
47 STAR\*D trial indicate poorer treatment response to SSRIs in those with atypical depression  
48 and therefore, statins could provide genuinely novel therapeutic targets for this group of  
49 people with TRD [17].

50

51 We plan to carry out an RCT involving 150 participants with treatment-resistant depression,  
52 with the aim of determining whether the addition of simvastatin (20mg daily), a lipophilic  
53 statin that readily crosses the blood-brain barrier [18, 19], to treatment as usual (TAU) for 12  
54 weeks leads to a reduction in depressive symptoms compared with placebo added to TAU.  
55 We predict that treatment-resistant depression patients will show improvement in mood with  
56 simvastatin treatment and that the response will be associated with reduction in lipid  
57 biomarkers (i.e. plasma LDL and LDL/HDL ratio). A secondary hypothesis relates to  
58 simvastatin's effects on putative inflammatory biomarkers. High LDL and low HDL  
59 contribute substantially to immunological up-regulation in the development of  
60 atherosclerosis. Pro-inflammatory cytokine (Interleukin-6 and Tumour Necrosis Factor)  
61 levels are often altered in depressed patients and decreased by successful antidepressant  
62 therapy [20, 21]. We therefore predict that in those treatment-resistant depression patients  
63 who show improvement in mood with simvastatin treatment, that response will be associated  
64 with reduction in inflammatory biomarkers. Our mechanistic hypothesis is that the anti-  
65 inflammatory and lipid-reducing effects of simvastatin will improve neuroinflammation and  
66 thus mediate a response to simvastatin.

67   **Methods**

68   A pragmatic multi-centre, 12-week, double blind, placebo controlled randomised trial of  
69   simvastatin added to treatment as usual (TAU) for patients suffering from a DSM-5 major  
70   depressive episode that has failed to respond to at least two trials of antidepressants. This will  
71   be a parallel group study with 75 participants in each arm. Recruitment will occur at  
72   outpatient psychiatric clinics in Karachi, Lahore, Hyderabad, Rawalpindi and Quetta  
73   Pakistan. Consistency of procedures across sites will be ensured through vigorous training  

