#### *Outcome measures*

The primary outcome measure will be the Montgomery-Asberg Depression Rating Scale (MADRS) [28] total score at week 12. Ratings will be made on the basis of a semi-structured clinical interview at baseline and at every follow-up visit until week 12. The MADRS was chosen as the primary outcome measure as it has been demonstrated to be more precise in estimating changes in depression severity compared to other measures [29, 30]. However the HRSD remains a useful screening tool and the use of different assessment scales at screening and follow-up mitigates the risk of clinician bias whereby raters over-estimate symptom severity at screening stage to increase study recruitment. This can then mask the true treatment effect and may lead to an inflated placebo response.

Other outcomes recorded will include the 24-item Hamilton Rating Scale for Depression (HRSD-24) [25] which includes assessment of atypical depressive symptoms, the Clinical Global Impression (CGI) scale [31], an overall measure of illness severity, the 7-item

Generalized Anxiety Disorder scale (GAD-7) [32], a self-report measure of severity for generalised anxiety disorder and a modified Morisky measurement of medication adherence (MMAS-4) [33]. We will also assess changes in body mass index (BMI) from baseline to week 12. All scales have been validated for use in the Urdu language and have been used in previous studies in Pakistan [24]. Adverse effects will be monitored using a side effect assessment scale based on the product monograph of simvastatin.

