#### *Measurement of biomarkers*

Participants will be asked to provide two blood samples: at baseline and week 12. We aim to analyse the relationship of simvastatin to lipid and inflammatory markers and determine if this is associated with symptom change prior to a clinical effect (if detected). The biomarkers analysed will include lipid biomarkers HDL, LDL and C-Reactive Protein (CRP), a peripheral marker of inflammation.

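### The named arm comparisons of lipids and CRP use raw change; no baseline-adjusted week-12 difference is named for these markers

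*Protocol*

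**What the plan says.** - **Background.** The hypotheses paragraph says "A secondary hypothesis relates to" "simvastatin's effects on putative inflammatory biomarkers". The prediction it then gives is narrower: in patients who improve on simvastatin, "that response will be associated" with a fall in the inflammatory markers.
- **Measurement of biomarkers.** The aim is given as "We aim to analyse the relationship of simvastatin to lipid and inflammatory markers", together with a link to symptom change. On sampling it says "Participants will be asked to provide two blood samples: at baseline and week 12".
- **Outcome measures.** After the MADRS, the list begins "Other outcomes recorded will include the 24-item Hamilton Rating Scale for Depression" and continues with CGI, GAD-7, MMAS-4 and BMI. Lipids and CRP are not in it.
- **Statistical Analysis, general rule.** Secondary analyses use mixed models like the primary one, adjusted for baseline, with week 12 as the main timepoint. Biomarkers are not mentioned.
- **Statistical Analysis, lipid/CRP mediation paragraph.** A descriptive step comes first. It will "look at the bivariate association between treatment group and change in lipid/CRP levels" (no timepoint is attached to this comparison) and will also relate marker change at weeks 4 and 12 to MADRS change. A mediation model follows, with a treatment effect on week-4 marker change.
- **Table 1.** Biomarkers are ticked at baseline, week 4 and week 12.

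**The concern.** Whether simvastatin shifts LDL, HDL and CRP relative to placebo is a randomised comparison, and the mechanistic hypothesis presupposes that it does. Where the protocol names a method for this comparison, the method is raw change, either descriptively or as a component of the mediation model. Raw change is less precise than follow-up adjusted for baseline, and a chance difference between arms at baseline feeds into it through regression to the mean. The plan already has a better model and already collects the baseline value.

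At stake is the clarity of the mechanistic results. The protocol itself warns that a mediated effect would have to be fairly large to be found at this sample size. If mediation is not shown, a clean week-12 arm difference with its interval would help the reader judge whether the drug moved the marker at all.

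**Working it through.** **Sample size used below.** The protocol plans 120 patients followed up, from 150 randomised, for a MADRS effect of 0.60 SD, two-sided alpha 0.05 and 90% power. Normal approximation: n per arm = 2(1.960 + 1.282)²/0.60² = 58.4, so 59 per arm and 118 in total. The t-test version gives 60 per arm, 120 in total (power 90.3%). Dropout: 120/(1 − 0.20) = 150. The plan's figures reproduce and do not depend on the biomarker analysis. I take 120 as the number with both blood samples, which is an assumption.

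**Not in the protocol.** It gives no biomarker SD, no baseline-to-follow-up correlation r and no biomarker power. I assume r from 0.4 to 0.8.

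**Equal SDs.** Per patient, in units of the variance:
- raw change: 2(1 − r)
- follow-up adjusted for baseline: 1 − r²
- efficiency of raw change: (1 − r²)/[2(1 − r)] = (1 + r)/2, so the loss is (1 − r)/2

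| r | Efficiency | Loss | 120 on raw change are worth | Extra patients for equal precision |
|---|---|---|---|---|
| 0.4 | 0.70 | 30% | 84 | 43% |
| 0.5 | 0.75 | 25% | 90 | 33% |
| 0.6 | 0.80 | 20% | 96 | 25% |
| 0.7 | 0.85 | 15% | 102 | 18% |
| 0.8 | 0.90 | 10% | 108 | 11% |

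**Unequal SDs.** Let k be the follow-up SD divided by the baseline SD. The loss is 1 − k²(1 − r²)/(1 + k² − 2rk), which simplifies to (1 − rk)²/(1 + k² − 2rk).
- k = 0.8: 46% at r = 0.4, 36% at r = 0.8
- k = 1.2: 18% at r = 0.4, 0.3% at r = 0.8

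The numerator is a square, so the loss is never negative. In large samples adjustment is never the worse choice, but the size of the gain depends heavily on k.

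**Baseline imbalance.** With equal SDs, a baseline difference d between arms shifts the raw-change comparison by −(1 − r)d. With 60 per arm, the standard error of d is √(2/60) = 0.183 SD. An imbalance of that size shifts the result by 0.6 × 0.183 = 0.110 SD at r = 0.4, and by 0.2 × 0.183 = 0.037 SD at r = 0.8. The standard errors of the raw-change comparison are 0.200 and 0.115 SD. At r = 0.4 the adjusted standard error is 0.167, and √(0.167² + 0.110²) = 0.200. The precision loss and the carried imbalance are therefore one quantity, seen before and after the baseline values are known.

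**The case against.** The other side has real weight.

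- **The general rule may already cover the markers.** It is not expressly limited to the listed outcomes, and a hypothesis called secondary could fall under it. If so, the adjusted week-12 contrast is already planned and nothing is lost. A reader might infer that the protocol plans no baseline-adjusted biomarker estimate; the documents support only that none is named. Against this, the lipid/CRP paragraph is the more specific text and sets out a different method.
- **The descriptive step is not the only comparison.** The mediation model formally estimates the treatment effect on week-4 change. So the documents do not support saying that the markers get only a descriptive look, or that a negative mediation result could not be interpreted. But that path is at week 4, also uses change, and depends on a blood sample about which the protocol contradicts itself.
- **The Background prediction is an association** between response and marker reduction, not an arm contrast at week 12. That is right. The point therefore rests on the wider aim under Measurement of biomarkers.
- **Week-12 marker data do have another stated use,** in relation to MADRS change. That is also right.
- **Assigning markers to models is usual SAP content.** Silence alone would be no finding. The protocol is not silent, however: it names a weaker method for this comparison.

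**Conclusion.** The point holds in limited form. The arm comparisons named for the markers use raw change, no baseline-adjusted week-12 difference is named, and the protocol does not settle whether its adjusted model applies. Following the specific text would cost 30% to 10% of the information for r from 0.4 to 0.8 with equal SDs. It would be tempting to quote that range as a property of this trial, but it is conditional: the documents give neither r nor the SDs, and at SD ratios of 0.8 and 1.2 the loss over the same r runs from 46% down to 0.3%. The formula also applies to whichever scale is analysed, so for a skewed marker such as CRP it is only a rough guide on the raw scale.

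This is lost precision, with chance baseline imbalance carried into the estimate. It is not a systematic bias under randomisation, it concerns a secondary and mechanistic analysis, and it does not touch the MADRS result or the sample size. The change is worth making because it is almost free.

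**What to change.** 1. State that LDL, HDL and CRP (CRP on the log scale) are analysed with the baseline-adjusted model already set out for secondary analyses, and report the week-12 arm difference with its 95% CI.
2. Include the baseline marker as a covariate in the treatment-to-biomarker path of the mediation model. Once baseline is in the model, change and follow-up give the same treatment coefficient, so the change definition can stay.
3. Keep the raw-change table as a descriptive supplement.
4. State whether these markers belong to the family covered by the family-wise correction for multiple measures.
5. Reconcile Measurement of biomarkers (baseline and week 12) with Statistical Analysis and Table 1 (week 4 included) before using a week-4 value. If there is no week-4 sample, there is a single post-baseline value per patient and an ANCOVA at week 12 replaces the repeated-measures model. The week-4 mediation path could then not be fitted as written.

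The cost is a few sentences in the protocol or SAP and a few extra model fits. Items 1 to 4 need no patients, visits or samples beyond those planned.
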